**Methods/Design:**

This trial is a two arm, single-blind, randomized controlled feasibility trial within in-patient stroke rehabilitation. We will recruit 80 patients receiving stroke rehabilitation in two stroke units in a health board area of Scotland (40 patients in each arm). Intervention arm participants will receive a visual-arts based CEI facilitated by experienced artists. Artists will follow an intervention protocol with specific components that enable participants to set, achieve and review artistic goals. Participants will receive up to eight intervention sessions, four within a group and four one-to-one with the artist. Control group participants will receive usual care only.

Data collection will occur at baseline, post-intervention and three-month follow-up. Stroke-related health status is the primary outcome; mood, self-esteem, self-efficacy, perceived recovery control and hope are secondary outcomes. Semi-structured interviews will be conducted with purposively selected patients, artists and healthcare staff to elicit views and experiences of the intervention and feasibility and acceptability of trial processes. Recruitment rates, retention rates and patient preference for art participation will also be collected. Data will indicate, with confidence intervals, the proportion of patients choosing or refusing participation in the CEI and will allow calculation of recruitment rates for a future definitive trial. Summary data will indicate potential variability, magnitude and direction of difference between groups. Findings will inform sample size calculations for a definitive trial. Thematic analysis of qualitative data will be managed using the Framework Approach. Framework is an analytical approach for qualitative data, commonly used in policy and medical research.

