### Trial procedures

Once participants meeting inclusion criteria have provided informed consent to participate, one of two study researchers will collect data indicating participant characteristics and will undertake baseline assessments. Stratification factors will be entered into the concealed online randomization system by the study researchers, who will inform the artists of group allocation. Participants in the intervention group will be invited to attend one individual and one group intervention session per week with the artist, for up to a maximum of eight sessions. The art portfolios will be delivered to participants allocated to the control group after baseline assessment.

A third researcher, blinded to group allocation and trained to administer outcome measures, will undertake outcome assessment with participants in the intervention group after eight art sessions, or at hospital discharge, if that occurs beforehand. The blinded researcher will undertake outcome measures with the control group at four weeks, or at discharge if that occurs prior to four weeks. Participants will be instructed not to reveal their group allocation to this researcher, but any episodes of un-blinding will be recorded. Three months after outcome assessment, the researcher will contact participants to arrange a follow-up assessment, which will be conducted in hospital or at the participants’ home, depending on discharge status. Nine participants from the intervention group and three from the control group, purposefully selected to reflect age, disability and gender, will also be invited to participate in audio-recorded in-depth interviews after follow-up assessment to evaluate their experiences of participation in the CEI, and the trial.

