#### Mood

The Positive and Negative Affect Scale [42] is a 20-item self-report measure comprising 10 positive and 10 negative affective descriptors. Measurement reliability has been examined; for the Positive Affect (PA) Scale, the Cronbach alpha coefficient was 0.86 to 0.90 and for the Negative Affect (NA) Scale it was 0.84 to 0.87 [39]. Over eight weeks the test-retest correlations were 0.47 to 0.68 for the PA and 0.39 to 0.71 for the NA. Strong correlation with measures of general distress and dysfunction, depression and state anxiety have also been reported [39]. Participants are asked to score the items on a five-point scale [1–5] ranging from ‘very slightly or not at all’ to ‘very much or extremely’ to indicate their emotions in the last week. The positive and negative affect scales each have a potential range of 10 to 50, where higher scores indicate higher affect. The scale has high validity and reliability for use in rehabilitation [43].

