### Sample size calculation

This is a feasibility trial therefore we have not undertaken a formal sample size calculation. A sample size of 40 participants in each group will be adequate to provide estimates of direction and magnitude of any effects, and to provide an estimation of variability for later sample size calculation. Previous literature shows that a sample size of between 30 and 36 per arm is adequate for a feasibility trial [55]. We based our sample size on that information, on our knowledge of likely participants to the art program, and on information from our previous experience of likely drop-out rates from stroke rehabilitation trials.

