### Statistical analysis

The Montreal Cognitive Assessment and the National Institutes of Health Stroke Scale will provide screening data and indicate baseline status. Other baseline characteristics to be collected are: age, sex, handedness, ischemic or hemorrhagic stroke, side of hemiplegia, Barthel Index, Aphasia Severity Rating Scale [56] and use or not of psychotropic medication. Preference for randomization to the intervention group (participating in art) or the control group (viewing art) will be assessed after randomization.

Data analysis will be undertaken blind to group allocation. The primary analysis will be based on the intention-to-treat principle. Proportions of missing data will be examined to inform decision-making about selection of outcome measures for the definitive trial. Transformations of the outcome variables will be used where necessary if these are not normally distributed. All analyses will incorporate the stratification factors.

Data will indicate, with confidence intervals, the proportion of patients choosing or refusing participation in the CEI and will allow calculation of recruitment rates for a future definitive trial. Data about the proportion of study dropouts will also provide information that will inform a definitive trial. Summary data from measures will indicate potential variability, magnitude and direction of difference between groups at the end of intervention and at three-month follow-up.

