To examine the effects of the intervention, a repeated measures analysis using mixed models will be conducted for outcomes, although these will not involve definitive hypotheses testing. Adjustment for baseline factors and mediating variables will be undertaken by adding these as covariates to give an idea of which factors are important in determining outcome. This will indicate where the intervention effects are likely to occur and will generate power calculations for a future definitive RCT. The measure with greatest difference as well as most relevance in the feasibility study will be selected as primary outcome measure, whilst taking into account proportions of missing data. Missing data will be examined for randomness, and if appropriate, multiple imputations will be conducted to replace missing values. Intention-to-treat analysis based on outcome evaluation of cases as randomized will be conducted to examine any important differences in findings. Reporting of results will adhere to Consolidated Standards of Reporting Trials criteria for the reporting of randomized controlled trials [57].

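### The model meant to supply effect sizes and power calculations adds mediators alongside baseline factors and does not ensure conditioning on each measure's own baseline score

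*Protocol article*

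**What the plan says.** The abstract gives the schedule: "Data collection will occur at baseline, post-intervention and three-month follow-up". Under Trial procedures, after consent and before allocation, "one of two study researchers will collect data indicating participant characteristics and will undertake baseline assessments". Each outcome's baseline score is therefore planned for every participant.

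Under Statistical analysis, "a repeated measures analysis using mixed models will be conducted for outcomes", without definitive hypothesis testing. The article does not say whether baseline is one of the repeated responses or a covariate. The next sentence reads: "Adjustment for baseline factors and mediating variables will be undertaken by adding these as covariates", with the aim of learning which factors matter for outcome. The modelling is then said to show where effects are likely and to produce the power calculations for a definitive trial.

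The same section requires every analysis to include the stratification factors (age band, gender and Barthel band, within site, under Randomization). It also lists baseline variables: "Other baseline characteristics to be collected are: age, sex, handedness, ischemic or hemorrhagic stroke, side of hemiplegia, Barthel Index", followed by aphasia severity and psychotropic medication. No outcome scale is on that list.

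The mediators are not named there. The Outcome measures section presents recovery locus of control, self-efficacy and hope as constructs that may explain how art works.

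**The concern.** Estimating effect size is a stated objective, and the future primary outcome is to be chosen partly by which measure shows the greatest difference. The model behind those figures therefore matters even without formal testing.

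The sentence on adjustment raises two problems. First, it treats baseline factors and mediators alike. Adjusting for a baseline variable leaves the treatment effect intact. Adjusting for a variable that the intervention may itself change does not.

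Second, the measure's own baseline score, usually the strongest single predictor available, is neither named nor excluded. At 40 per arm a chance baseline difference in a self-report scale can be sizeable. If it is not conditioned on, part of it passes into the follow-up difference, and choosing the measure with the largest difference then favours scales that happened to start unbalanced.

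**Working it through.** There is no planned calculation to reproduce: "This is a feasibility trial therefore we have not undertaken a formal sample size calculation". The article gives no alpha, power, effect or SD.

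**Inputs**
- n = 40 per arm: "A sample size of 40 participants in each group will be adequate to provide estimates of direction and magnitude of any effects". All 80 are taken as analysed; any dropout widens every interval.
- Correlation ρ between baseline and follow-up: not given. Test-retest values serve as proxies. For mood: "Over eight weeks the test-retest correlations were 0.47 to 0.68 for the PA and 0.39 to 0.71 for the NA". For the Stroke Impact Scale the article cites intra-class correlations of 0.7 to 0.92, with 0.57 for the emotion domain; for self-esteem, 0.80 and above. I use 0.39, 0.5 and 0.7 as the main range.
- Assumptions: three visits, equal variances and equal correlations, complete data, no covariates other than baseline.

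**Mediators.** Let c be the total effect, a the effect of the intervention on the mediator, and b the effect of the mediator on the outcome given group. In a linear model, adding the post-randomisation mediator changes the group coefficient from c to c − ab. The residual variance also loses what the mediator explains. Effect and SD then both belong to a different question from the one a definitive trial of the total effect would ask. The documents give no a or b, so the size cannot be stated. A baseline value of the same scale would do no such harm, but the article does not say which measurement is meant.

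**Chance imbalance.** The SE of a baseline difference is √(2/40) = 0.224 SD. In a follow-up comparison without baseline, a fraction ρ of it carries over: 0.39 × 0.224 = 0.087 SD, or 0.7 × 0.224 = 0.157 SD, for a one-SE imbalance.

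**Precision of the final-visit effect.** SE in units of SD × √(2/40):
- no baseline: 1
- own baseline as covariate: √(1 − ρ²)
- baseline as a response with a common mean (constrained): √(1 − ρ²), identical
- baseline as a response, unconstrained, effect read as group by time: √(2(1 − ρ))

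| ρ | covariate or constrained | unconstrained | no baseline ÷ covariate | unconstrained ÷ covariate |
|---|---|---|---|---|
| 0.39 | 0.921 | 1.105 | 1.09 | 1.20 |
| 0.5 | 0.866 | 1.000 | 1.15 | 1.15 |
| 0.7 | 0.714 | 0.775 | 1.40 | 1.085 |

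The last column is √(2/(1 + ρ)); at 0.7, √(2/1.7) = 1.085.

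As 95% half-widths at 40 per arm: 0.445 SD without baseline, against 0.410, 0.386 and 0.318 SD with the covariate.

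**Planning.** For an assumed standardised difference of 0.5, two-sided 5% and 90% power, n per arm is 85 with the raw SD. With the residual SD it is 72, 64 and 43 at the three correlations.

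**The case against.** The strongest reply is that this is a condensed article, that an exact covariate list normally belongs in the SAP, and that nothing in the text excludes the baseline score. The phrase about baseline factors may well include it. A repeated measures model over three visits may carry it as a response, and in constrained form that gives up no precision. All of this stands.

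A reader might infer that intervals will certainly be wider and the planning SD certainly larger. The documents do not support that: the loss runs from nil to the figures above, depending on how baseline enters. A reader might also infer that planning will rest on unadjusted summary data. The article never calls the summary data unadjusted, and it attributes the power calculations to the modelling. The comparator of 0.445 SD also ignores the stratification factors. These include Barthel band, and the article reports a high correlation between the Barthel Index and the Stroke Impact Scale, so the real contrast for that scale may be smaller.

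It can also be said that the article does not state that mediators enter the main effect model. That is fair, but no separate model is described. The sentence joins the two kinds of covariate, and the modelling as a whole is then said to feed the power calculations. This is a positive statement that could be followed as written, not just a detail left out.

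**Conclusion.** The point holds in a limited form. As written, the adjustment sentence allows post-randomisation mediators into the model that supplies effect sizes and planning figures. That would condition away part of the effect, by an amount the documents do not let one calculate.

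The text also leaves own-baseline conditioning unsecured. For ρ of 0.39 to 0.7, omitting baseline would make intervals about 9 to 40% wider than own-baseline adjustment. An unconstrained baseline response would make them about 20% (at 0.39) down to 8.5% (at 0.7) wider, and a constrained one would lose nothing. The figures rest on test-retest values as proxies. Correlations over recovery may be lower, which would reduce the loss from omitting baseline but increase the relative loss from the unconstrained model. Since baseline scores will be collected, the precision loss is recoverable if it is noticed before the planning figures are used.

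**What to change.** State that effect estimates and planning SDs come from a mixed model of the two post-randomisation assessments, with the same measure's baseline score and the stratification factors as covariates, or from an equivalent constrained-baseline model. Report the residual SD and the baseline-to-follow-up correlation for each measure. Place mediators in separate exploratory analyses that do not feed the effect size or the power calculation.

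The change is to wording and needs no new data. It costs one degree of freedom per outcome and a stated way of handling missing baseline scores, which may occur because completion of the measures is itself under study.

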Confidence that personal rehabilitation goals and art-specific goals could be achieved was generated through the opportunities for skill acquisition that art provided. Confidence was inferred by the qualitative study as a route by which art participation improved recovery, self-esteem and mood. We therefore included a measure of general self-efficacy [49–52] and one that examines self-efficacy for art [46], to evaluate whether art improves self-efficacy and influences more distal outcomes, such as stroke recovery. Perceptions of difficulty can also influence self-efficacy therefore a single-item measure to assess difficulty has been included, as suggested by Francis *et al*. [52].

Hope appears to predict better rehabilitation outcomes. Hope occurs when a person perceives routes to achieving goals and has motivation to access those routes [53, 47]. It has been hypothesized that in rehabilitation hope buffers negative emotions because the individual believes that goals can be achieved despite obstacles [48, 54]. Hope was another concept that our qualitative interviews suggested was developed through art participation. We therefore included the Hope Trait Scale [47] as a secondary outcome. The scale measures hope agency thinking, which represents a patient’s wilful sense of determination to meet goals, and pathway, which reflects a patient’s perceived availability of ways to attain a goal.

This is a pilot trial, therefore as well as clinical and psychological outcomes, we are also collecting data on other outcomes that relate to the feasibility of conducting a definitive trial. We will collect data and evaluate trial recruitment rates, the proportion of participants who prefer to be randomized to art and retention and dropout rates. We will examine the variability of scores on outcome measures and completion rates and ease of use of the chosen measuring instruments at each assessment point. We will also undertake comparison between the measures to determine which are more appropriate for use in a definitive trial. Finally, we will evaluate with participants and staff, the acceptability and feasibility of undertaking the trial in rehabilitation settings.

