## Discussion

There is growing interest in the role that participation in the arts can provide in healthcare settings. Evidence is also emerging that art participation can augment rehabilitation, help to address the psychosocial effects of stroke and prepare survivors for fulfilling lives after rehabilitation. Providing such an intervention in rehabilitation settings is potentially costly, therefore its effects should be evaluated in the same way as other healthcare interventions, using robust scientific methods. Furthermore, assuming that art participation is a valuable adjunct to rehabilitation, it is vital that we seek to understand how it works and the outcomes that it influences. In line with other rehabilitation interventions, such understanding will enable us to refine the intervention to target it at those most likely to derive its known benefits.

However, the creative and apparently subjective nature of art participation means that designing a trial to test its effects is challenging. Our preparatory qualitative work based on the Medical Research Council’s (MRC) Framework for complex intervention design has enabled us to define the stages of the CEI and to provide a framework that is replicable, based on the core elements of an existing program. Our study endorses the importance of qualitative preparatory work as a precursor to trial design for complex interventions. This work enabled us to define the ways in which the intervention appears to work and the outcomes it appears to influence. The feasibility trial will enable us to undertake preliminary testing of these hypotheses and to determine feasibility issues associated with undertaking a trial of this nature in rehabilitation settings. Furthermore, qualitative interviews with participants at the end of the trial will enable us to confirm or disconfirm the effects of the CEI and our selection of outcome measures, and to refine the design of a full-scale definitive RCT.

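### Adding baseline factors and mediating variables as covariates shows what is associated with outcome, not where the intervention effect occurs, and is not a sound source of power inputs

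*Protocol article*

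**What the plan says.** The second half of the Statistical analysis section describes the models in this order:

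- The intervention effect is examined by mixed models for repeated measures, not intended as definitive tests: "a repeated measures analysis using mixed models will be conducted for outcomes, although these will not involve definitive hypotheses testing".
- Baseline factors and mediating variables are then added to these models, "by adding these as covariates to give an idea of which factors are important in determining outcome".
- The next sentence states what follows: "This will indicate where the intervention effects are likely to occur and will generate power calculations for a future definitive RCT".
- The sentence after that turns to the choice of outcome: "The measure with greatest difference as well as most relevance in the feasibility study will be selected as primary outcome measure".

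Earlier in the same section, the stratification factors are to be included throughout: "All analyses will incorporate the stratification factors".

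Two other places bear on the meaning. The Outcome measures section includes the self-efficacy measures "to evaluate whether art improves self-efficacy and influences more distal outcomes, such as stroke recovery", and lists recovery locus of control and hope as further secondary outcomes representing constructs through which art might work. The Discussion hopes that "such understanding will enable us to refine the intervention to target it at those most likely to derive its known benefits".

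The sample is 40 per arm. The Sample size calculation section says no formal calculation was made, and the article gives no SD, effect size, significance level or correlation.

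**The concern.** Read in sequence, the covariate step is what is said to show where the intervention acts and to supply the power calculations. It can do neither safely.

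- **Which patients.** With a factor added but no arm-by-factor term, the model assumes the same intervention effect at every level of that factor. The factor's coefficient describes its association with outcome given arm.
- **Which constructs.** A coefficient for hope or self-efficacy in a model for health status shows that the two go together. It does not show that art changed hope or self-efficacy.
- **Which outcome measures.** The arm contrast answers this. But once mediating variables are in the model, the arm coefficient no longer need be the total effect, which is what a definitive trial would be powered on.

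At stake is the design of the next trial. Ordinary prognostic factors could be taken for places where art works, and the effect size and SD carried forward could belong to a different quantity.

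**Working it through.** The article states no figure to reproduce, so the check is of the inference itself.

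**Inputs.** From the article: 80 patients, 1:1. Assumed: residual SD 1, two-sided 5% as the criterion for calling a factor important, and all effect sizes.

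**1. What an additive coefficient estimates.** Let the factor's slope on outcome be β in controls and β + γ in the art arm, so γ is the effect modification. With equal arms and the factor balanced across them, the coefficient in a model with arm and factor only is the average slope, β + γ/2. One number cannot separate β from γ.

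Simulation with a balanced binary factor, 5,000 trials per row:

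| Truth | β + γ/2 | Mean additive coefficient | Additive term flagged | Interaction flagged |
|---|---|---|---|---|
| β = 0.8, γ = 0, no arm effect | 0.80 | 0.80 | 94% | 5% |
| β = 0.8, γ = 0, uniform arm effect 0.5 | 0.80 | 0.80 | 94% | 5% |
| β = −0.5, γ = 1.0, arm effect 0.5 | 0 | 0.00 | 5% | 59% |
| β = 0, γ = 0.5, arm effect 0.5 | 0.25 | 0.25 | 20% | 19% |

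Rows 1 and 2 show that the flag does not depend on whether the intervention works. Row 3 is chosen so that the slopes cancel; it shows that real modification can be invisible. Row 4 shows that the coefficient does pick up half of a modification, but nothing marks it as such.

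A second simulation used a continuous factor, the mean of two post-baseline visits with within-person correlation 0.6, and 4,000 trials per scenario. With no effect modification, a factor correlated 0.2, 0.3, 0.4 or 0.5 with outcome was flagged in 51%, 86%, 98% and 100% of trials at 40 per arm. The interaction rejected in 4% to 5%. These percentages are simply the power to detect an association that was assumed to exist.

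**2. Constructs.** In the second set-up, for a construct that allocation does not change, its coefficient in the outcome model was significant in 85% (r = 0.3) to 100% (r = 0.5) of trials. The arm difference in the construct itself was significant in 5%.

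**3. Power inputs from a model containing a mediator.** Assume that allocation moves the mediator M by 0.5, that M moves the outcome by 0.5 per unit, that there is a direct effect of 0.25, and that both residual SDs are 1.

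- Without M: effect = 0.25 + 0.5 × 0.5 = 0.50; SD = √(1 + 0.5²) = 1.118; standardised 0.50/1.118 = 0.447.
- With M: effect = 0.25; residual SD = 1; standardised 0.25.
- Ratio of required sample sizes = (0.447/0.25)² = 3.2.

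A simulation of this example gave effects of 0.50 and 0.25 and SDs of 1.12 and 1.00. The size and direction of the distortion depend on the assumed paths; the example shows only that the two quantities differ.

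**4. What an interaction could deliver at 80 patients.** For a balanced binary factor, SE = 4 × SD/√N = 4/√80 = 0.447.

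- Power for an interaction of 0.5 SD: Φ(0.5/0.447 − 1.96) = Φ(−0.84) = 20%.
- Interaction detectable with 80% power: (1.96 + 0.84) × 0.447 = 1.25 SD.
- Overall arm effect detectable with 80% power: (1.96 + 0.84) × 2/√80 = 0.63 SD.

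**The case against.** The strongest reply is that the sentence asks in which outcome measures effects occur, not in which patients. The paragraph opens with intervention effects across outcomes, and the next sentence chooses a measure. The Background lists the outcomes likely to be influenced as an open question, and the Study aims want effect sizes to guide the choice of primary outcome. Covariate coefficients alone could not feed a power calculation, so the arm contrasts must be included in what is meant. This reading is plausible and the text does not exclude it. It does not rescue the sentence, because the contrast would then come from a model that conditions on mediating variables.

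Three further replies stand:

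- Self-efficacy, recovery control and hope are secondary outcomes in their own right, so the arm difference in each is largely planned already.
- Treatment-by-factor terms may sit in an analysis plan that is not shown. Their absence is not the point; the stated inference is.
- The simulated rates rest on assumed effects and an assumed significance criterion. The article says only that the covariates give an idea of what matters.

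A reader might infer something stronger: that the trial will report prognostic factors as places where art works and will choose the next trial's population from them. The documents do not support that. No rule links covariate results to a target population. The Discussion's remark on targeting follows from understanding how art works and what it influences, and announces no subgroup analysis. The misreading is possible, not planned.

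**Conclusion.** The point holds in limited form. On either reading, the covariate step is not what shows where the intervention effect occurs. If patients are meant, additive covariates cannot answer the question. If outcome measures are meant, the answer and the power inputs belong to the randomised contrast without mediating variables.

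That an additive coefficient cannot separate prognosis from effect modification is algebra and needs no assumed effect size. The rates (94% against 5%, and 51% to 100%) and the halved arm effect are illustrations under assumed values. The part on power inputs also assumes that the mediating variables enter as values measured after randomisation, which the word mediating suggests but the article does not spell out.

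Severity is minor to moderate: the analysis is declared non-definitive and the wording is ambiguous, but its results are meant to shape the definitive trial.

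**What to change.** In the Statistical analysis section:

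1. Describe covariate coefficients as prognostic only.
2. State that where effects are likely to occur is judged from the arm contrast for each outcome, with self-efficacy, recovery control and hope counted as outcomes in their own right. An arm difference in a construct is necessary for it to be a mechanism, but not sufficient.
3. Take the effect size and SD for the power calculation from the model with baseline and stratification factors but without mediating variables.
4. Only if patient subgroups are meant, name a few baseline factors already collected (for example age, sex and Barthel Index) and report arm-by-factor interactions as exploratory estimates with 95% confidence intervals, without selection by significance.

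The cost is a few sentences and some extra model fits, with no new data. Any interaction estimates will be imprecise at 80 patients, as shown above, and should stay descriptive.
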